## Statistical analysis

The baseline distribution of sociodemographic and clinical characteristics in each treatment arm will be reported using descriptive statistics.

The main hypothesis of the change in the time to relapse (in weeks) will be analyzed using Cox regressions, and the hypotheses of the changes in the scores of clinical scales as compared to baseline will be tested using repeated measures analyses of variance (ANOVAs) that will include time, treatment arm and their interaction. Those variables that show statistically significant between-arm differences at baseline will be added as covariates in the Cox regressions and repeated measures ANOVAs. For each of the analyses effect size measures (hazard ratio or Hedges’ *g*) will be estimated.

An intention-to-treat (ITT) analysis will be employed to provide unbiased comparisons among the treatment groups, using multiple imputations to deal with the losses of follow-up.

R software will be used to carry out the statistical analyses.

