### Study aim

The overall aim of this study is to examine whether the EMDR Bipolar protocol for BP with a history of traumatic events can reduce affective relapses, improve affective and trauma-related symptoms and result in a better performance in cognition and psychosocial functioning, when compared ST. Other related aims of this trial are to expand the available options for psychosocial intervention in BD, to explore that the EMDR therapy is a safe and effective tool in traumatized bipolar patients and that treatment with EMDR leads to an improvement in the course and prognosis of the disease.

Based on our pilot study of EMDR in traumatized bipolar patients, we propose the following hypotheses:The EMDR group will show fewer affective relapses at 12 and 24 months’ follow-up compared to the ST groupPatients in the EMDR group will show fewer affective and trauma-related symptoms compared to the ST group at evaluations after 6 months of therapy, at 12 and 24 monthsPatients in the EMDR group will show a better cognitive and psychosocial functioning compared to the ST group at evaluations after 6 months of therapy, at 12 and 24 months

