### Trial design

This is a single-blind, randomized controlled clinical trial with two parallel branches, EMDR and ST. Patients will be matched for age, sex, illness duration and number of affective episodes the year before the clinical trial. The primary outcome variables that are affective relapses, symptoms of trauma and cognition and psychosocial functioning, will be assessed at six time points; pretreatment (T0), mid-treatment at 2 weeks (T1) and at 3 months (T2), post treatment at 6 months (T3), and follow-up evaluations at 12 (T4) and 24 months (T5) (see Fig. 1). The secondary outcome variables that are the course and prognosis of the disease, will be assessed in follow-up evaluations at 12 (T4) and 24 months (T5). The research assistants conducting the clinical assessments will be blind to the participants’ research condition. Patients are not blind to treatment as it is impossible for a therapist to offer and for a patient to receive therapy without being aware of the techniques that they are using orreceiving. The study has been approved by the Ethics Committee of the Germanes Hospitalàries del Sagrat Cor de Jesús (reference number: PR-2014-15), the Hospital Clínic of Barcelona (reference number: HCB/2015/1005) and the Hospital del Mar (reference number: 2015/6502/l). All participants will sign informed consent prior to enrollment. Details of the trial design can be also gathered from Additional file 1 (Standard Protocol Items: Recommendations for Interventional Trials (SPIRIT) flow diagram) and the SPIRIT Checklist (Additional file 2).

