### Assessments

Demographical and clinical variables will be collected through an interview using the medical history of the patients and a specific Case Report Form (CRF) for the study, including sex, age, age of onset of the disorder, number of relapses, number of previous episodes, history and number of suicide attempts previous and current pharmacological treatment, family background and consumption of drugs. To ensure privacy of participants and safe data storage, data will also be entered in a data file anonymously; participants will be given a unique number, and only the research assistant will be able to link the number with the name of the patient. At baseline (T0) research assistants will also assess clinical severity of affective symptoms, presence of traumatic live events and trauma symptoms, and cognitive and psychosocial functioning. At 2 weeks (T1) and 3 months (T2) of treatment patients will be evaluated with respect to clinical symptoms. After the treatment phase (T3) subjects will be interviewed with respect to clinical symptoms, trauma scales, cognitive and psychosocial functioning and patient satisfaction. During two follow-up visits at 1 year (T4) and 2 years (T5), blind-to-treatment evaluators apply clinical affective and trauma scales, functioning and cognition. See Fig. 1 (flow diagram of enrollment, intervention and assessments).

The clinical severity will be assessed by means of different instruments (see Table 1):

**Table 1 Tab1:** Measurements to evaluate clinical variables

Clinical variable	Measurement interview/Self-report	T0	T1	T2	T3	T4	T5
		Baseline	Mid-treatment		Post treatment	FU 12 months	FU 24 months
Mania	Young	x	x	x	X	x	x
Depression	BDRS	x	x	x	X	x	x
Severity	CGI-BP-M	x	x	x	X	x	x

*FU* Follow-up, *YMRS* Young Mania Rating Scale, *BDRS* Bipolar Depression Rating Scale, *CGI-BP-M* Clinical Global Impression Scale modified for bipolar disorder

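### The planned time-by-arm ANOVA does not directly test the 6-, 12- and 24-month hypotheses for the scale outcomes, and it leaves the baseline score unadjusted

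*Protocol article*

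**What the plan says.** All references are to the protocol article.

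- **Test.** Under Statistical analysis, "the hypotheses of the changes in the scores of clinical scales as compared to baseline" are to be "tested using repeated measures analyses of variance (ANOVAs) that will include time, treatment arm and their interaction".
- **Covariates.** The only adjustment rule there is data-driven: "Those variables that show statistically significant between-arm differences at baseline will be added as covariates". The baseline value of the scale has no planned place in the model otherwise.
- **Effect sizes.** "For each of the analyses effect size measures" are promised, with Hedges' g for the scales, but g is not tied to a visit.
- **Hypotheses.** Under Study aim, hypotheses 2 (affective and trauma symptoms) and 3 (cognition and functioning) place the EMDR versus ST comparison "at evaluations after 6 months of therapy, at 12 and 24 months".
- **Visits.** Under Assessments, "At 2 weeks (T1) and 3 months (T2) of treatment patients will be evaluated with respect to clinical symptoms". Table 1 therefore has the mood scales (YMRS, BDRS, CGI-BP-M) at all six visits. Tables 2 and 3 have CAPS, IES-R, SUD, SCIP, MSCEIT and FAST at T0, T3, T4 and T5.

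**The concern.** The named test and the stated hypotheses have different targets. A time-by-arm interaction asks whether the two mean profiles differ in shape anywhere. Hypotheses 2 and 3 ask whether EMDR is better than ST at three named visits. A significant interaction does not say which arm did better or when, and on the mood scales it can be driven by visits outside the hypothesis.

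An analysis of change that does not condition on the baseline score is also generally less precise than one that does, and with about 36 patients per arm precision is scarce.

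Every conclusion on mood, trauma, cognition and functioning rests on this test. Trial design even counts trauma symptoms, cognition and functioning among the primary outcome variables.

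**Working it through.** **Inputs.** The analysable sample is n = 36 per arm, 72 in total (Computation of sample size). That figure was derived for the Cox regression. The article gives no sample size or power for the scales, so there is no figure of its own to reproduce here. The visit schedule comes from Tables 1 to 3. The following are assumptions, because the article gives none of them: within-patient correlation rho of 0.3, 0.5 or 0.7; an arm difference of 0.5 SD; two-sided alpha of 0.05; compound symmetry for the F test.

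**Step 1: what the interaction detects.** With T0 as a level of time, the interaction has 6 − 1 = 5 df for the mood scales and 4 − 1 = 3 df for the others. For arm differences d_t in SD units, the noncentrality is

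λ = (n/2) × Σ(d_t − mean d)² / (1 − rho).

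*Effect only at 2 weeks and 3 months, none at 6, 12 or 24 months.* Here d = (0, 0.5, 0.5, 0, 0, 0), so Σ = 2 × 0.25 − 6 × (1/6)² = 0.333. At rho 0.5, λ = 18 × 0.333 / 0.5 = 12.0. On 5 and 350 df the test is significant with probability 0.76 (0.75 by simulation). At rho 0.3 and 0.7 the probability is 0.59 and 0.95.

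*Effect only at 24 months, rho 0.5.* The omnibus test has power 0.53 with six visits and 0.56 with four. A single unadjusted change contrast at 24 months has 0.55, and a baseline-adjusted contrast has 0.68.

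The omnibus test is therefore about as powerful as one unadjusted change contrast. Its fault is the target.

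**Step 2: precision of one arm contrast.** Let σ0² be the baseline variance, β the slope of follow-up on baseline and σe² the residual variance. Per patient:

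- change score: (1 − β)²σ0² + σe²
- baseline-adjusted: σe²

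The first is never smaller than the second, apart from the one degree of freedom spent on the slope. If baseline and follow-up variances are equal (both 1), then β = rho, the two become 2(1 − rho) and 1 − rho², and their ratio is (1 + rho)/2.

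| rho | change | adjusted | ratio adjusted/change | 72 × ratio | power, change | power, adjusted |
|---|---|---|---|---|---|---|
| 0.3 | 1.40 | 0.91 | 0.65 | 46.8 | 0.42 | 0.59 |
| 0.5 | 1.00 | 0.75 | 0.75 | 54.0 | 0.55 | 0.68 |
| 0.7 | 0.60 | 0.51 | 0.85 | 61.2 | 0.77 | 0.83 |

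The column 72 × ratio is the number of patients analysed with adjustment who would carry the same information as 72 analysed as change scores. Power is for 0.5 SD at one visit.

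**Step 3: BDRS and YMRS.** Under Participants, entry is limited to BDRS below 14 and YMRS below 12. Selecting on baseline shrinks σ0² but, in a linear model, leaves β and σe² unchanged, so the equal-variance ratio does not apply. As an illustration, take unit variances before selection, so that σe² = 1 − β², and then halve the baseline SD (σ0² = 0.25):

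- β = 0.3: 0.91 / (0.49 × 0.25 + 0.91) = 0.88
- β = 0.5: 0.75 / (0.25 × 0.25 + 0.75) = 0.92
- β = 0.7: 0.51 / (0.09 × 0.25 + 0.51) = 0.96

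For these two scales adjustment removes roughly a tenth of the variance or less.

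**The case against.** **The article does not say that T0 is a level of time.** This is correct; it is the natural reading of changes from baseline tested in a time-by-arm model. If change scores were the outcome instead, the df would be 4 and 2, and a benefit held constant over follow-up would fall in the arm main effect. Baseline would still be unadjusted and no visit would be named.

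**Contrasts and sphericity corrections are detail that a condensed article may leave out.** This is partly right. A model with categorical visits contains the contrasts at T3, T4 and T5, and an analysis plan could extract them. But the article names the ANOVA as the test of these hypotheses and fixes the covariate rule, so such a plan would have to change the published method and not merely fill it in.

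**Three stronger readings are tempting but not supported.**

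- A reader might infer that the narrow entry range of mood scores makes a change analysis especially costly for BDRS and YMRS. Step 3 shows the reverse. At β = 0.5 with the baseline SD halved, the correlation falls to 0.5 × 0.5 / √0.8125 = 0.28. The equal-variance formula would then give 0.64, where the ratio is 0.92.
- A reader might infer that the omnibus test throws away power. Step 1 does not show that. For a 0.5 SD benefit sustained over T3 to T5 at rho 0.5, the six-visit interaction has power 0.82, more than a single adjusted contrast.
- A reader might infer an inflated type I error from non-sphericity. Simulations of the uncorrected test with decaying correlation gave about 5% to 9.5%, depending on how the correlation decays. The article does not say that no correction will be used.

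**Conclusion.** The point stands in a moderate form. The named test does not directly address the 6-, 12- and 24-month arm differences, and on the mood scales it can be significant because of visits outside the hypothesis.

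The loss of precision is real in direction but uncertain in size. The adjusted variance is 0.65 to 0.85 of the change-score variance for rho 0.3 to 0.7 if baseline and follow-up variances are equal. That is more plausible for trauma, cognition and FAST, though SUD has an entry floor of its own. The ratio is about 0.9 for BDRS and YMRS. No correlation or variance is given for any scale, so these are ranges under stated assumptions. Using a tighter alpha than 0.05 would lower every power figure above.

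The Cox analysis of relapse is not affected.

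**What to change.** Replace the repeated-measures ANOVA with a mixed model for repeated measures on the post-baseline scores. Include baseline score, baseline-by-visit, arm, visit and arm-by-visit, with unstructured covariance, whether or not the arms differ at baseline. This also removes the sphericity assumption. Keep T1 and T2 in the model for the mood scales, but test hypotheses 2 and 3 by the arm contrasts at T3, T4 and T5. Report each with a confidence interval and Hedges' g, stating the SD used to standardise it. The planned multiple imputation may be kept.

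The cost is analysis wording and standard R code; no new data are needed. There is one small downside. Nine scales are measured repeatedly, so three contrasts each give 9 × 3 = 27 comparisons. The plan should state how multiplicity is handled, consistent with the correction for multiple comparisons mentioned under Computation of sample size.

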## Methods/design

This multicenter collaborative project will involve the participation of three different centers from the Barcelona catchment area, Spain (Hospital Benito Menni, Hospital Clinic of Barcelona and Hospital del Mar). EMDR and supportive therapy (ST) therapists have extensive experience in the application of both psychotherapies. EMDR therapists have already participated in the pilot study [24] and all therapists received a detailed day training in applying the EMDR therapy protocol and a well-defined ST program. The application of all clinical assessments has been defined and practiced within all participating raters. All centers and research groups involved have wide ambulatory facilities and outpatient clinics for BD patients that will facilitate meeting the recruitment criteria and development of this project.

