### Randomization procedure

All patients meeting the inclusion criteria receive the pretreatment (T0) assessment. After T0, participants will be assigned to EMDR or the ST group by two independent researchers using the following covariate-adaptive allocation procedure [26]: (1) the first two patients will be randomly allocated to EMDR or ST with *p* = 0.5, (2) the next patients will be allocated as follows: (b1) if one group already includes two more patients than the other group, the patient will be randomly allocate to EMDR or ST with *p* = 0.8 for the smallest group and *p* = 0.2 for the largest group, (b2) otherwise, we will first simulate that the patient is allocated to EMDR and calculate the sum of the between-group square standardized differences in age, sex, illness duration and number of affective episodes the year before the clinical trial between groups, we will then simulate that the patient is allocated to ST and recalculate the sum, and finally randomly allocate the patient to EMDR or ST with *p* = 0.8 for the group with the smallest sum and *p* = 0.2 for the group with the largest sum. For example, if we had already included 10 patients to the EMDR group and 8 patients to the ST group, the 19th patient would be randomly allocated with *p* = 0.2 for EMDR and *p* = 0.8 for ST. If they were allocated to ST, we would calculate the above sum of covariates after simulating that the 20th patient is allocated to EMDR and after simulating that is allocated to ST, and if the sum of the EMDR simulation was larger than the sum of the ST simulation, we would randomly allocate the 20th patient with *p* = 0.2 for EMDR and *p* = 0.8 for ST. Following this procedure, final groups should be balanced in size and matched in age, sex, duration and episodes. All steps of the randomization process will be automatically carried out in a central location using a computer program.

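### The baseline-significance screen for covariates will almost never admit the four factors that the allocation balances, so the analysis ignores the allocation scheme and, if those factors are prognostic, loses power

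*Protocol article*

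**What the plan says.** The primary analysis is a Cox model: "The main hypothesis of the change in the time to relapse (in weeks) will be analyzed using Cox regressions". Scale scores go to repeated measures ANOVAs with terms for time, arm and their interaction. Covariates enter both by one rule: "Those variables that show statistically significant between-arm differences at baseline will be added as covariates in the Cox regressions and repeated measures ANOVAs". The only other route into the models is in the Limitations section, which says that pharmacological treatment will be taken into account, without saying how.

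The Randomization procedure assigns patients "using the following covariate-adaptive allocation procedure". Unless one arm already leads by two patients, the program computes the sum of the "between-group square standardized differences in age, sex, illness duration and number of affective episodes the year before the clinical trial" under each possible assignment. It then favours the arm giving the smaller sum with probability 0.8. The stated expectation is that "final groups should be balanced in size and matched in age, sex, duration and episodes". The Trial design section also says that patients will be matched on these four variables. No section places them in any model.

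**The concern.** The two rules work against each other. The allocation makes the arms alike on four chosen variables, and the analysis admits a variable only if the arms are unlike on it. The variables thought important enough to balance are thus the ones least likely to be adjusted for.

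Balancing a prognostic factor reduces the true variability of the treatment comparison. A model that omits the factor does not use that reduction: its standard error is too large for the design, and its test rejects too rarely. In a Cox model, omitting a prognostic factor also moves the estimated hazard ratio toward 1.

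Among the remaining baseline variables, a significance test under randomisation picks up only chance differences. What enters then depends on chance rather than on prognostic value. At stake is power for the primary hypothesis in a trial with none to spare.

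**Working it through.** **The plan's own figure.** No figure is attached to the covariate rule. The only power statement is in Computation of sample size: 36 per group for hazard ratio 2, 80% power, alpha 0.005. Schoenfeld's formula (two-sided) gives 4 × (2.807 + 0.842)² / (ln 2)² = 4 × 13.31 / 0.4805 ≈ 111 events, more than the 72 patients, so the figure is not reproduced. That is a separate matter. It is relevant here only because it shows there is no reserve of power.

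**Inputs to the simulation.**
- From the protocol: the allocation algorithm (first two patients at 0.5, then 0.8/0.2 on arm size or on the covariate sum), 82 patients, 24 months, hazard ratio 2 (taken as 0.5 for EMDR), alpha 0.005, and 2 to 6 episodes at entry.
- Assumed: 70% control relapse at 24 months. The Background gives almost 70% within 2 to 4 years, so this is the early end.
- Assumed: the covariate distributions and prognostic strengths, for which the protocol gives nothing. Log hazard ratios per SD for age, sex, illness duration and episodes were: none (all 0); weak (0, 0, 0.05, 0.2); moderate (0, 0, 0.1, 0.4); strong (0.15, 0.1, 0.3, 0.6).
- Runs: 3000 per setting (2000 for weak and for the sensitivity settings). Dropout and multiple imputation were not simulated. The screen was applied to the four factors only, at p < 0.05.

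**Does the screen admit the factors?** With 82 patients, none of the four reached p < 0.05 in any of 3000 runs. With 72 patients, at least one did in 0.2% of runs. Under simple randomisation at 82, at least one did in 18%. For these factors the protocol rule is in effect the unadjusted Cox model.

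**Consequence** (82 patients; protocol rule vs always adjusting for the four):

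| Prognosis | Type I error, nominal 5% | Power, alpha 0.05 | Power, alpha 0.005 | Mean HR, true 0.50 |
|---|---|---|---|---|
| None | 5.0% vs 6.0% | 64.8% vs 66.7% | 30.6% vs 32.5% | 0.495 vs 0.483 |
| Weak | 4.3% vs 5.3% | 63.1% vs 66.3% | 28.8% vs 32.5% | 0.502 vs 0.482 |
| Moderate | 3.3% vs 5.5% | 59.2% vs 65.8% | 23.7% vs 32.4% | 0.519 vs 0.481 |
| Strong | 2.4% vs 5.3% | 48.7% vs 65.5% | 15.1% vs 32.0% | 0.558 vs 0.479 |

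Differences at 0.05: 66.3 − 63.1 = 3.2, 65.8 − 59.2 = 6.6 and 65.5 − 48.7 = 16.8 points. At 0.005: 3.7, 8.7 and 16.9 points.

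Under simple randomisation the unadjusted test kept its level (4.9 to 5.1%), so the conservatism comes from ignoring the adaptive allocation. The shift in the hazard ratio does not: it also appeared under simple randomisation (0.562 in the strong case) and comes from omitting prognostic covariates.

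**Sensitivity** (moderate prognosis, alpha 0.05): with 50% control relapse and 82 patients, 45.2% vs 51.5%; with 85% relapse and 72 patients, 62.2% vs 68.9%.

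**Events available for adjustment.** Expected events per pair of patients, one in each arm: 0.70 + (1 − 0.30^0.5) = 0.70 + 0.452 = 1.152. With 41 per arm, 41 × 1.152 ≈ 47; with 36 per arm, 36 × 1.152 ≈ 41.

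**Chance entries.** With about 15 other baseline variables, the chance that at least one is significant would be 1 − 0.95^15 = 54% if they were independent. The trauma scales overlap with each other, as do the affective scales, so 54% is an upper-end figure.

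**The case against.** **The size rests on assumption.** This stands. The protocol does not say how strongly any of the four factors predicts relapse. The strong case needs a log hazard ratio of 0.6 per SD for episodes, whose range at entry is only 2 to 6. A reader might infer a certain and large loss of power. The documents support only a conditional one, close to zero if the factors are not prognostic. Their choice as balancing factors suggests that they are thought to matter, but that is not a figure.

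**Part of the gain is not real.** This also stands. The adjusted test runs slightly above nominal (5.3 to 6.0% in the main setting). With no prognostic effect at all it still shows 66.7 − 64.8 = 1.9 points more power. More than half of the 3.2 points in the weak case may be small-sample inflation. The moderate and strong losses clearly exceed it.

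**The rule is prespecified and uses no outcome data.** Correct. A reader might infer outcome-driven model selection or inflated false positives. Neither follows: the screen looks only at baseline, and for the four factors the error is in the conservative direction.

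**Other covariates can enter.** A reader might take the screen as the sole route, but the Limitations section gives pharmacological treatment a route of its own. That is not a balancing factor, so the conflict remains.

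**Centre.** The trial has "the participation of three different centers from the Barcelona catchment area", and a reader might count the silence on centre as a further error. Centre is not an allocation factor, and an article may leave that detail to the analysis plan.

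That last defence does not cover the screen itself. It is a stated rule, which a later analysis plan would have to replace rather than complete.

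**Conclusion.** The concern holds as a conflict between the Statistical analysis section and the Randomization procedure. It is near-certain, though not absolute given the 0.8/0.2 random element, that the primary Cox model will be unadjusted for the four factors on which patients are allocated.

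If those factors are prognostic, the test is conservative, the hazard ratio is attenuated and power is lost, within the ranges tabulated above. Those ranges rest on assumed covariate distributions and strengths, a 70% control relapse rate at 24 months, and complete follow-up. The same reasoning applies to the repeated measures ANOVAs, but no size was computed for them. The trial stays interpretable without the change; it is weaker than it needs to be.

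**What to change.** Replace the screening sentence in the Statistical analysis section with a fixed rule:

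- The Cox and repeated measures models include age, sex, illness duration and number of affective episodes in the preceding year as prespecified covariates.
- No covariate is selected by a baseline significance test, and the baseline table is descriptive.
- The section states how pharmacological treatment enters the models, so that it agrees with the Limitations section.

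Stratification by centre is not part of this change. Nor is the baseline score as an extra covariate where T0 is already a level of time, since that would use the same measurement twice.

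The cost is a short change of text. The allocation program already needs all four variables, so nothing new is collected. The price in the model is four added terms on roughly 41 to 47 expected events under the assumed rates. With the treatment term that is about 8 to 9 events per term (41/5 to 47/5). This is acceptable, but the plan should say so and acknowledge the slight excess over nominal type I error seen in the simulation.
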